**Fig 1 Fig1:**
[figure not shown]
Theory of Change for COMPASS

Caregivers will also participate in monthly discussion groups which seek to increase knowledge of the needs of adolescent girls. The goals are to ultimately shift gender-inequitable attitudes about girls in the home and increase support to keep girls safe within and outside of the home. This content is delivered by IRC program staff. The incremental effectiveness of this caregiver component is being tested in DRC, while in Ethiopia we are evaluating the overall COMPASS program effectiveness.

In addition, COMPASS will engage health service providers and case managers to train workers on Clinical Care for Sexual Assault Survivors [28] and Caring for Child Survivors Guidelines [29] in order to improve the overall quality of services for adolescent girl survivors of violence in their communities. Additional activities will be undertaken to engage communities to support girls as well.

### Randomization, sample size, and power analysis

Based on the assumptions of 80 % power to detect a Cohen’s effect size of d = 0.3 between treatment versus wait-list groups (α < 0.05 statistical significance level, a design effect of 2.0), a sample size of 704 girls is required in each country. After accounting for an expected attrition rate of 25 % in DRC, the final sample size required at least 880 girls and a total of 886 girls were surveyed at baseline. Primary caregivers of selected girls in DRC were also asked to participate in the study (n = 777 surveyed at baseline). In Ethiopia, given movement concerns within the refugee camps and higher likelihood of loss to follow-up and potential refusals at baseline, the attrition rate was inflated and a total of 919 girls were surveyed at baseline.

Groups are comprised of 20–25 girls each, based on geographic proximity or language. Groups of girls were divided into younger groups and older groups, given age-tailored content of programming. In DRC, 35 girl groups across 14 villages in South Kivu were divided into two age strata: 10–12 years of age and 13–14 years of age. In Ethiopia, 47 groups across three refugee camps were divided into age strata; group formation also accounted for school scheduling in the camps. Groups were first stratified by age level (13–14 years and 15–19 years) and then randomized to either the intervention or wait-list arm following the baseline survey. If sisters or girls who identified the same caregiver or reside in the same house were participating in the program, girls were assigned to the same group if they were in the same age category. If they were in separate age groups, the groups were paired together and randomized to the same study arm. Randomization was completed using the statistical software R version 3.2.1.

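### DRC sample size: 880 does not retain the required 704 girls after the stated 25% attrition; 939 would be needed

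*Protocol article*

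**What the plan says.** All the figures stand in one section of the protocol article, Randomization, sample size, and power analysis. The starting point is "Based on the assumptions of 80 % power to detect a Cohen’s effect size of d = 0.3", with "α < 0.05 statistical significance level, a design effect of 2.0", and the result is that "a sample size of 704 girls is required in each country".

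For DRC the article continues: "After accounting for an expected attrition rate of 25 % in DRC, the final sample size required at least 880 girls". It then reports that "a total of 886 girls were surveyed at baseline".

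For Ethiopia it cites movement in the camps, a greater chance of loss to follow-up and possible refusals at baseline, and says that "the attrition rate was inflated and a total of 919 girls were surveyed at baseline". It gives no Ethiopian attrition rate, no calculated Ethiopian target and no inflation formula for either country.

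**The concern.** An allowance for attrition is meant to ensure that the required number remains after the expected loss. Loss applies to the girls enrolled, so the required number must be divided by the proportion retained. Multiplying it by one plus the loss rate gives too few, and the stated DRC figure matches that multiplication exactly.

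Two things are at stake. First, the printed DRC minimum is a design figure that readers will rely on, and it does not do what the sentence says. Second, the article names displacement and mobility as leading retention concerns. A team that trusts 880 would take 25% loss in DRC as fully covered, when the number surveyed covers less than that. Ethiopia raises the same question, because its number surveyed is only 33 above DRC's (919 − 886) while its expected loss is described as higher.

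**Working it through.** **Inputs, all from the sample size section of the article:** power 80%, d = 0.3, alpha 0.05, design effect 2.0, 704 required per country, 25% attrition in DRC, 886 surveyed in DRC, 919 surveyed in Ethiopia, 35 groups in DRC and 47 in Ethiopia. Two-sided testing and 1:1 allocation are not stated; I assume both because together they reproduce 704.

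**1. Reproduce 704.** A two-sample t-test with these inputs needs 175.4 girls per arm, rounded up to 176. Then 176 × 2 arms × 2.0 = 704, an exact match. (The normal approximation gives 175 per arm and 700 in total.) So 704 is the number needed for analysis and contains no attrition allowance. Power at 704 is 80.1%.

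**2. Reproduce 880.**
- 704 × (1 + 0.25) = 880, an exact match.
- 704 / (1 − 0.25) = 938.7, so 939. This does not match.
- 704 / (1 − 0.20) = 880. This matches, but at 20% loss, not the stated 25%.

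**3. Girls retained in DRC at 25% loss.**
- 880 × 0.75 = 660, which is 44 short of 704.
- 886 × 0.75 = 664.5, about 40 short.
- Largest loss that 886 can absorb: 1 − 704/886 = 20.5%.
- The stated minimum is 939 − 880 = 59 girls too low, or 59/939 = 6%.

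**4. Ethiopia, by inference.**
- Largest loss that 919 can absorb: 1 − 704/919 = 23.4%.
- At DRC's 25%, used here as an assumption: 919 × 0.75 = 689, about 15 short.

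**5. Power at 25% loss, design effect held at 2.0.** Two-sided t-test, effective number per arm = N/(2 × 2.0):

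| | Girls retained | Power |
|---|---|---|
| Target | 704 | 80.1% |
| DRC, 886 surveyed | 664.5 | 77.8% |
| Ethiopia, 919 surveyed | 689 | 79.3% |

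If Ethiopian loss were 30% or 35% (both assumptions), 643 or 597 girls would remain and power would be 76.5% or 73.4%.

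**6. Sensitivity to the fixed design effect.** The number of groups is fixed, so attrition shrinks the groups, and the design effect 1 + (m − 1) × ICC falls with group size m. The article gives neither the ICC nor the group size behind 2.0. I therefore take two readings, with equal group sizes:

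| 2.0 refers to | Country | Implied ICC | m after 25% loss | Design effect | Power |
|---|---|---|---|---|---|
| Groups as enrolled | DRC (886/35 = 25.3) | 1/24.3 = 0.041 | 19.0 | 1.74 | 83% |
| Groups as enrolled | Ethiopia (919/47 = 19.6) | 1/18.6 = 0.054 | 14.7 | 1.74 | 85% |
| Groups after attrition | DRC (704/35 = 20.1) | 1/19.1 = 0.052 | 19.0 | 1.94 | 79.0% |
| Groups after attrition | Ethiopia (704/47 = 15.0) | 1/14.0 = 0.072 | 14.7 | 1.98 | 79.8% |

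The shortfall in girls retained does not depend on these readings. Whether power falls below 80% does.

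**The case against.** **The formula is not shown.** True, so the multiplication is inferred. The inconsistency does not rest on it: 75% of 880 is 660, below 704, whatever route was taken.

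**The power consequence is small and uncertain.** This stands. A reader might infer that the 80% power claim fails in both countries. The documents do not support that. With the design effect fixed at 2.0, the drop from 80.1% is about 2 points in DRC and under 1 point in Ethiopia at 25% loss. If 2.0 describes the groups as enrolled, power at 25% loss stays above 80% in both countries.

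**No Ethiopian error is shown.** This also stands. The 919 is a count of girls surveyed, not a calculated target, and part of the inflation was for baseline refusals, which had already happened by the time 919 was counted. A reader might infer that Ethiopia misses its own target at its own planned attrition, but that rate is not printed. What can be said is narrower: 919 protects 704 against less loss than DRC's stated rate, in a setting where more loss is expected.

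**A corrected DRC power figure could mislead.** This stands as well. The section on quantitative assessment says that in DRC only girls aged 13–14 were asked the violence modules. A power figure based on about 664 girls therefore does not describe the DRC analysis of past-year sexual violence, the primary outcome.

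**Baseline is complete, so nothing changes.** Enrolment cannot usefully change, but the statement can be corrected, and the tolerable losses can still guide retention work before endline.

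**Conclusion.** The concern holds for DRC as an arithmetic inconsistency. The printed 704, 25% and 880 cannot all be right, and nothing elsewhere in the article corrects them. At 25% loss the requirement is 939. The stated minimum leaves 660 and the 886 surveyed leave about 664, so 704 is preserved only up to 20.5% loss. This rests only on printed figures and on reading 704 as the number needed after attrition, which the exact reproduction of 704 supports.

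For Ethiopia the conclusion is an inference: 919 preserves 704 only up to 23.4% loss, and the actual planned rate is unknown.

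The effect on power is modest and conditional on the design effect. The correction is worth making because the figure is wrong as written; it does not undermine either trial.

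**What to change.** In the sample size paragraph:

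1. Correct the DRC requirement to 939 girls at 25% attrition. If the allowance was really 20%, keep 880 and correct the rate.
2. State that the 886 and 919 girls surveyed preserve 704 only up to 20.5% and 23.4% loss respectively, and give the rate actually planned for Ethiopia.
3. If power at the planned attrition is quoted, say that it holds the design effect at 2.0 (about 78% in DRC at 25% loss; about 79% in Ethiopia at an assumed 25%). Say also that it applies to outcomes measured in all girls, not to the DRC sexual-violence outcome asked only of those aged 13–14.
4. Do not re-open enrolment.

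The cost is a few corrected figures in one paragraph and a slightly less favourable statement of the attrition margin. No design or analysis step changes.

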In Ethiopia, ACASI was used for the entire survey due to challenges of hiring female enumerators who can both speak the local non-written languages selected for the study (Engsena Quickly, Funj/Berta, Maban, or Regarig) and read and write in Amharic, Arabic or English. ACASI was selected as a data collection method as it has been shown to increase reporting of sensitive behaviors [31] in addition to its ability to overcome the language and literacy challenges found among refugee camps in Western Ethiopia. Colors and images for response options were piloted and varied by country in the final ACASI programming.

Descriptive statistics and tests of variables of interest, including chi-square tests and t-tests, will be constructed. Generalized linear mixed models, also known as hierarchal/multilevel mixed models, will be used to assess whether girls in the intervention arm report changes in outcomes of interest compared to girls in the intervention arm, accounting for multiple levels of clustering in the data (time, family, group, village/refugee camp zone). Intention-to-treat analyses and per protocol analyses, based on attendance records, will be generated.

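### Linked younger and older groups were randomised together, but the planned mixed model names no level for the jointly randomised set, so the arm effect's standard error can be too small

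*Protocol article*

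**What the plan says.** Under Randomization, sample size, and power analysis, girls from one household or with one caregiver are kept in one arm by two rules. Within an age stratum, "girls were assigned to the same group if they were in the same age category". Across strata, "If they were in separate age groups, the groups were paired together and randomized to the same study arm". The article counts 35 groups in 14 villages in DRC and 47 groups in three camps in Ethiopia. It does not say how many were linked.

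Under Quantitative assessment and analytic plan, generalized linear mixed models carry the comparison of arms, "accounting for multiple levels of clustering in the data (time, family, group, village/refugee camp zone". The sentence before it reads: "Descriptive statistics and tests of variables of interest, including chi-square tests and t-tests, will be constructed". The same section restricts the violence questions in DRC to the older stratum.

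The Discussion adds that allocation took place within communities in DRC and within small areas of the camps in Ethiopia.

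**The concern.** A cluster-randomised analysis should recognise the unit that was allocated. Here that is a single group where there is no link and a set of groups where there is one. The article states both the allocation rule and the list of model levels, and the two do not match. Wherever groups were linked, 35 and 47 overstate the number of independently allocated units.

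The listed levels repair this only in part:

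- A family effect covers the linked girls, not the other girls in a group of 20–25.
- A village or zone effect covers shared location. But arms are contrasted within village or zone, and variation shared by a linked set inside one village does not cancel from that contrast.
- Groups were formed by proximity or language, so some likeness within a set below zone level is credible, though not shown.
- A family that spans the age strata belongs to two groups. A model nesting family strictly within group would split those sisters.

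At stake are p-values and intervals that treat linked groups as separately assigned. Chi-square and t-tests without cluster adjustment would be worse if used to compare arms.

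**Working it through.** **1. The plan's own figure.** Inputs are "80 % power to detect a Cohen’s effect size of d = 0.3 between treatment versus wait-list groups" and "α < 0.05 statistical significance level, a design effect of 2.0". A two-sided test and 1:1 allocation are assumed.

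- Normal approximation: n per arm = 2(1.960 + 0.842)²/0.3² = 174.4, so 175; 175 × 2 × 2.0 = 700.
- Two-sample t version: 175.4, so 176 per arm; 176 × 2 × 2.0 = 704.

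This reproduces "a sample size of 704 girls is required in each country".

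**2. Implied intracluster correlation.** Taking the design effect (DE) of 2.0 to refer to single groups (not stated), ρ = 1/(m − 1). That is 1/19 = 0.053 at m = 20 and 1/24 = 0.042 at m = 25. At the midpoint m = 22.5, ρ = 1/21.5 = 0.0465 and mρ = 1.047.

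**3. Treating paired groups as independent.** Let f be the share of groups that are paired, and r the correlation between girls in different groups of a pair, divided by ρ. Both are assumed.

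- DE = 1 + (m − 1)ρ + f·r·mρ = 2.0 + 1.047·f·r
- SE ratio (true/assumed) = √(DE/2)
- Type I error = 2[1 − Φ(1.96/SE ratio)]

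| f | r | DE | SE ratio | Type I error | Power at 704, correct SE | N for 80% power |
|---|---|---|---|---|---|---|
| any | 0 | 2.00 | 1.00 | 5.0% | 80% | 702 |
| 0.25 | 0.25 | 2.07 | 1.02 | 5.4% | 79% | 725 |
| 0.5 | 0.5 | 2.26 | 1.06 | 6.5% | 75% | 794 |
| 1 | 0.5 | 2.52 | 1.12 | 8.1% | 71% | 886 |
| 1 | 1 | 3.05 | 1.23 | 11.2% | 63% | 1069 |

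The first row shows 702 because 175.4 per arm is not rounded up before multiplying. The table leaves village/zone out of the model and covers simple pairs, not chains.

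**4. With a village/zone level in the model.** A simulation of group means (600 runs per scenario, z-test) fitted village/zone and group effects but no pair effect. It used 35 groups in 14 villages for DRC, as for an outcome measured in both strata, and 47 groups in an assumed 12 zones for Ethiopia. Each cell gives the empirical/model SE ratio, with type I error in brackets.

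| Pairing | Between-group variance: pair / village-zone / group | DRC layout | Ethiopia layout |
|---|---|---|---|
| none | four splits | 0.98–1.07 (5.0–8.2%) | 0.99–1.03 (5.7–6.8%) |
| all | 0 / 0.5 / 0.5 | 1.01 (8.3%) | 1.04 (6.3%) |
| all | 0.25 / 0.25 / 0.5 | 1.06 (6.8%) | 1.07 (7.5%) |
| all | 0.5 / 0 / 0.5 | 1.11 (9.2%) | 1.21 (11.2%) |
| all | 0.5 / 0.25 / 0.25 | 1.17 (11.7%) | 1.18 (11.5%) |

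Simulation error is about 1/√(2 × 600) = 0.03 on a ratio and √(0.05 × 0.95/600) = 0.9 percentage points on a 5% rate. The no-pairing row shows that noise and the small-sample z-test account for part of the excess. Only the last two rows stand clearly above it.

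**5. Unadjusted tests.** At a design effect of 2.0 the true SE is √2 = 1.41 times the naive one, so type I error is 2[1 − Φ(1.96/1.41)] = 16.6% at a nominal two-sided 5%.

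**6. Which outcomes.** A simple DRC pair joins a 10–12 group to a 13–14 group, and only the latter answers the violence questions. The pair then supplies one group to the primary outcome, and r plays no part. In Ethiopia both strata (13–14 and 15–19) answer.

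**The case against.** The case against is substantial, and much of it stands.

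- A reader might infer that the model clusters on single groups alone. It does not: family and village/zone are listed too, and they take up the sisters' correlation and shared location.
- A reader might infer that standard errors will be too small. The documents do not support that. If linked groups share nothing beyond family and village/zone there is no understatement, and the moderate simulated scenario cannot be told from noise.
- A reader might take the difference between 886 girls and 777 caregivers (109) as a count of links. It is not one. Caregivers were asked to take part, so the gap may include those who did not, and same-age sisters sit in one group and create no cross-group link.
- A reader might apply the figures to sexual violence in DRC. There only chains joining several older groups would matter, and the article speaks only of pairing.
- A reader might take the chi-square and t-tests as the treatment analysis. They are listed with descriptive statistics, and the next sentence gives the arm comparison to the mixed models.
- The degrees-of-freedom method and covariates are commonly left by an article to the analysis plan. Their absence is no error. Omitting a stratification factor usually makes inference conservative, if anything.

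What the objection does not remove is the mismatch. The levels are listed, the joint allocation is stated, and the jointly allocated set is not on the list.

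**Conclusion.** The mismatch between allocated unit and modelled levels is certain from the text. Its effect is uncertain. For simple pairs, type I error lies between 5% and about 11%, with the top value needing every group paired, full correlation within pairs and no village/zone term. This rests on a two-sided 5% test, equal allocation, groups of about 22.5 girls, a design effect defined on single groups, and assumed values of f and r. Chains of three or more groups are not covered by that bound.

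The point applies to the primary outcome in Ethiopia and to DRC outcomes measured in both strata. It reaches DRC sexual violence only through chained links. The 16.6% figure is conditional on unadjusted tests being used between arms, which the article does not say. The plan should still be corrected, because the remedy is specific and cheap.

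**What to change.** In Quantitative assessment and analytic plan:

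1. Add the randomised unit (the linked set of groups, or the single group where unlinked) as a clustering level for the arm comparison. Treat family as crossed with group or nested in the set.
2. Include the age stratum used in randomisation as a fixed effect, so that the model follows the design.
3. Base small-sample inference on the number of randomised units, for example by Kenward–Roger or Satterthwaite degrees of freedom. Report that number per arm and country.
4. State that chi-square and t-tests are descriptive only, or cluster-adjust any that compare arms.

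This changes wording, not design or data collection. The links were needed to carry out the randomisation, so they should be on file. The cost is that confidence intervals may be slightly wider.

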### Study population, recruitment, and retention

IRC program staff introduced the COMPASS program to the communities, and interested girls and their caregivers were invited to participate in the program. For example, in Ethiopia, outreach efforts included social worker house visits and ongoing activities at IRC Women and Girls Wellness Centers, which provide basic socioeconomic empowerment programming for women and girls in the camps and psychosocial services for survivors. Upon completion of program registration forms, girls (and their caregivers in DRC) were invited to participate in the studies. Eligibility criteria for the program and study varied by age and language based on contextual tailoring of adolescent girl programming across country sites. Details are provided in Table 2. In all sites, potential participants were excluded if they had cognitive impairment. Caregivers and girls were selected to participate in qualitative research activities based on purposive selection to generate a diversity of languages, ages, and schooling statuses.

**Table 2 Tab2:** Eligibility criteria for COMPASS girl research participants

	DRC	Ethiopia	Pakistan
Age	10-14 years	13-19 years	12-19 years
Language	Swahili	Engesena Quickly^a^	Pashtu
	Mashi	Funj/Berta	
		Maban	
		Regarig	

^a^Can also be termed Ingessana Kulag

Throughout the delivery of COMPASS, girls and their caregivers will be tracked by program mentors to improve and record retention through attendance records. Primary concerns for loss to follow-up for this study includes displacement, lack of buy-in from parents which could result in girls not being allowed to participate, and early marriage. Specifically, the latter is a concern because when girls marry, they may drop out of programming to undertake additional household duties. If a girl becomes married within the duration of the program, she will still be encouraged to participate by the mentors. In addition, if a girl has not attended programming, mentors will directly follow-up with the girl and caregiver and support her attendance. Reasons for non-attendance will be continually assessed by program and research teams; program delivery timing or other barriers to attendance will be addressed as possible. If there are multiple girls that miss more than three sessions within one group, IRC staff will engage directly with the mentor to support that mentor to improve retention of girls in her group.

Further, in Ethiopia, additional steps are planned to retain and track girls in the wait-list group, while minimizing risk of contamination. This tracking is also needed to determine whether girls have moved from the camps during the study period. These steps include checking in with girls during standard school-supply distributions approximately six months into the study and an additional check in with girls one month before endline data collection.

### Ethics

All study procedures were approved by the Columbia University Institutional Review Board (IRB) and by in-country local bodies (Ministry of Health, Gender, Family, and Humanitarian Affairs in South Kivu, DRC and Administration for Refugee and Returnee Affairs in Ethiopia). The study protocol for Ethiopia was also approved by the International Rescue Committee internal review board. All caregivers were asked to provide informed consent for the girls’ participation in the study if the girl was under 18 years old. Subsequently, girls were asked to assent for their participation in the study. In DRC, informed consent was read to potential participants through trained enumerators and written consent was given. Caregivers were also asked to provide written informed consent for their own participation in the quantitative survey and qualitative research activities. In Ethiopia, informed consent was administered via audio recordings because the languages selected for the study are non-written; thus, informed consent forms were verbally translated into the appropriate languages and recorded. All potential participants listened to the same audio recording to ensure consistency in the informed consenting process and provided verbal consent. Data collection staff were trained and available to respond to any questions on the consenting process. Since languages were non-written, only verbal consent/assent was required for participants in Ethiopia.

Given the highly sensitive nature of conducting research on the topic of violence against girls, all research staff completed training on the importance of ensuring confidentiality, privacy, and basic concepts of gender-based violence in accordance with the World Health Organization guidelines on violence against women research [30] and protocols for reporting breaches were developed. All enumerators were asked to complete confidentiality agreements. At the end of the interview, all participants were given information about where and how to receive additional services regarding violence and psychosocial support and referrals were made to service providers as needed.

